event after administration of the agent occurs, the clinical signs, symptoms, laboratory assessments, and other observations will be recorded. The adverse event will be assessed by the primary investigator to determine if the adverse event was caused by administration of the agent (see section 15 for definitions of causality). The intensity of an adverse event will be graded according to the NCI Common Toxicity Criteria v 5.0. Adverse events that cannot be graded using the NCI Common Toxicity Criteria will be graded as mild (asymptomatic), moderate (symptomatic but not interfering significantly with function) or severe (causing significant interference with function). The pharmacokinetics of Illuminare-1 will be evaluated. Dose levels of the agent will be administered starting at 0.25mg/kg, with increases in dose between cohorts of no more than 0.5 mg/kg until a maximum dose of 2.25mg/kg is reached, if needed. At the dose identified to have the acceptable NMR and no associated DLTs, Illuminare-1 will be studied in up to 20 additional patients at this dose to optimize the imaging protocol and provide additional safety data. Blood samples will be drawn at days 10 ( $\pm$  5 days) and 45 ( $\pm$  10 days) and stored for potential future research investigations under MSK IRB#06-107 or MSK IRB#12-245. Neurologic assessments, using the Neuropathy Impairment Scale – Lower Limbs and Beijers questionnaire for CTC Grading of Peripheral Neuropathy, will be performed at enrollment (baseline assessment), during hospitalization after surgery, and at the routinely scheduled postoperative visits at days 10 ( $\pm$  5 days) and 45 ( $\pm$  10 days). A phone follow-up will be made at 30  $\pm$  5 days. Video of the white-light and blue-light assessments of the nerves of interest will be recorded throughout the procedure and provided to the investigators and company sponsor for *post hoc* analysis for future hardware and software optimization. Twenty four hour ECGs will be collected via Holter monitor and stored for *post hoc* analysis.

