9. Adverse events will be recorded and reported as necessary for the first 24 h after injection or until discharge and at the first postoperative visit ( $10 \pm 5$  days). Adverse events will also be collected by phone at  $30 (\pm 5)$  days, and in person at the follow-up visit corresponding to the first postoperative PSA lab assessment, which typically occurs approximately 7 weeks after surgery ( $45 \pm 10$  days). Blood will be drawn at each in person follow-up visit for potential future research purposes under MSK IRB#06-107 or MSK IRB #12-245.

## Part 2

1. In this dose-expansion part of the study, we will continue to assess the safety of Illuminare-1 at the dose selected following completion of Part 1.
2. In this part of the study, we will evaluate, in addition to the obturator nerve, the neurovascular bundles before opening the endopelvic fascia and during the nerve-sparing portion of the prostatectomy (if performed as part of the standard of care surgery). We will look at the neurovascular bundles after removal of the prostate to see whether a fluorescent signal consistent with nerve structures within the neurovascular bundle can be identified. One surgeon observer will record whether presumed nerve structures are visualized under blue-light conditions (Yes vs. No); if nerve structures are seen, the confidence level of this assessment will be recorded (graded scale of 1-4, as described previously). The extent of surgery performed and the degree of nerve sparing that was undertaken will not be altered on the basis of the fluorescence of the

presumed location of the neurovascular bundles. This will be optionally performed during Part 1 if possible. The sensitivity and specificity of this agent's ability to accurately localize the small nerves within the neurovascular bundles have not been established, and no surgical decisions will be made on the basis of the fluorescence of structures in the periprostatic regions.

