11. Patients exposed to a photosensitizing agent may experience a phototoxic skin reaction, such as a sunburn, when exposed to excessive ultraviolet light or phototoxic drugs. As a precaution and because the half-life of the agent is approximately 4 hours, we will avoid administration of phototoxic drugs such as St. John's wort, griseofulvin, thiazide diuretics, sulfonylureas, phenothiazines, sulphonamides, quinolones, and tetracyclines for 24 hours before and after administration of Illuminare-1. These medications are uncommonly administered during the standard preoperative and postoperative pathway for patients undergoing minimally invasive radical prostatectomy.
12. Patients will be evaluated prior to discharge on postoperative day 1 and repeat neurologic examinations performed at baseline will be performed. Patient will also receive a CTN telephone call within 2 days of surgery for toxicity evaluation.
13. Patients will be evaluated at the postoperative visit on POD 10 (+/- 5). Repeat neurologic examinations performed at baseline will be performed. One tube of blood will be drawn for future research purposes under MSK IRB#06-107 or MSK IRB#12-245.

14. Patients will be evaluated at a postoperative visit on POD 30 (+/- 5) with a telephone follow-up. Patients are not routinely seen between the day 10 visit and the first PSA lab assessment so a telephone visit to assess for toxicity will be performed and if necessary, an in-person visit will be coordinated if there is clinical concern.
15. Patients will be evaluated at the postoperative visit on POD 45(+/- 10) corresponding to the first PSA blood level assessment. Repeat neurologic examinations performed at baseline will be performed. One tube of blood will be drawn for future research purposes under MSK IRB#06-107 or MSK IRB #12-245.

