| Urine culture (if indicated)                                | X |   |   |   |   |   |   |
| ECG                                                         | X |   | X |   |   |   |   |
| Research ECG via 24-hour Holter monitor †                   |   | X | X |   |   |   |   |
| Adverse events** CTCAE 5.0                                  |   |   | X |   | X | X | X |
| Neurologic assessment                                       | X |   | X |   | X |   | X |
| Subjective fluorescence assessment of obturator nerve       |   | X |   |   |   |   |   |
| Subjective fluorescence assessment of neurovascular bundles |   | X |   |   |   |   |   |
| Blood sampling for pharmacokinetics ***                     |   | X | X | X |   |   |   |
| PSA lab assessment*                                         |   |   |   |   |   |   | X |
| Blood for future research purposes (under 06-107 or 12-245) |   |   |   |   | X |   | X |
| Ex vivo tissue H&E                                          |   |   | X |   |   |   |   |
| Video evaluation (duration of surgery, NMR)                 |   | X |   |   |   |   |   |

\*Standard of care evaluations.

\*\*Serious adverse events will be reported from the time of informed consent to the end of study evaluation (45 +/- 10 days). Adverse events considered to be related to the drug that are grade ≥2 will be reported from the time of Illuminare-1 administration to the end of study evaluation. Adverse events from the time of informed consent to Illuminare-1 administration will be recorded in the medical history. Postsurgery (<24 hr) AE evaluation will occur via a CTN phone call within 2 days of surgery.

\*\*\*Blood will be drawn at baseline, 15, 30, 120, 240, 480 minutes (all +/- 10min), 12 hours (+/- 1h), 18 hours (+/- 2h), and 24 hours (+/- 2h) after injection for pharmacokinetics evaluation in all patients. In addition, a minimum of 3 patients in each dose cohort will also have blood drawn at 48 hours (+/- 24h) and 72 hours (+/- 24h) after administration for pharmacokinetics evaluation.

† ECG extraction timepoints: 3 baseline timepoints preoperatively; 0.25, 0.5, 2, 4, 8, 12 and 24 hours post-dose to align with PK timepoints. Patients to be comfortably resting in a supine position for ~10 minutes, the first 5 minutes to allow the heart rate and autonomic tone to stabilize, and the second 5 minutes for the ECG 'extraction window'. Exact timepoints will be recorded.

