Subjects will remain in the hospital after administration of Illuminare-1 for approximately 24 hours before discharge. During this period, the patients will be monitored for adverse events according to CTCAE 5.0 and undergo neurologic examination in addition to the two neurologic instruments for assessing peripheral nerve function, the Beijers questionnaire for CTC grading of peripheral neuropathy (Appendix B) and the Neuropathy Impairment Scale–Lower Limbs (Appendix A). These validated instruments will be used at the postoperative time points listed in the next paragraph below; if a change from baseline is identified, a full neurologic assessment will be performed to determine whether the change is considered to be related to the drug. These neurologic assessments are not part of the routine standard of care evaluations performed for patients undergoing minimally invasive radical prostatectomy and are being done as part of the safety profile assessment of the agent.

Following surgery, all adverse events will be evaluated at 10 ( $\pm$  5) days, at 30 ( $\pm$  5) days (additional telephone call primarily for toxicity assessment), and at 45 ( $\pm$  10) days after surgery (day of first PSA lab assessment and postoperative visit). We will record the number of subjects in each cohort who experience a DLT after receiving Illuminare-1. The entire follow-up period for patients on study will last no more than 45 ( $\pm$  10) days after surgery.

DLTs will be defined as follows, using NCI-CTCAE 5.0:

1. Hematologic Toxicity
  - a. Study treatment–related febrile neutropenia
  - b. Grade  $\geq$ 2 neutropenia lasting  $>$ 7 days
  - c. Study treatment–related grade  $\geq$ 2 thrombocytopenia or bleeding associated with grade  $\geq$ 2 thrombocytopenia
2. Nonhematologic Toxicity
  - a. Study treatment–related grade  $\geq$ 2 nonhematological toxicity
  - b. Any drug-related death

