#### 15.1.1.4. Additional Stopping Criteria

Individual Subjects will be withdrawn if they show poor tolerability with respect to signs and symptoms, clinically significant changes in laboratory parameters or vital signs.

Safety parameters from a given cohort will be fully assessed before dose escalation and escalation will proceed according to the dose escalation criteria outlined in the protocol. Any trends towards treatment-related changes will be fully evaluated.

Any subject with clinically significant changes in safety parameters not listed above or significant AEs thought to be treatment-related will be withdrawn from study treatment and

monitored until recovery. A full assessment by the primary investigator and/or the safety monitoring board will determine whether it is safe and ethical for the subject to continue.

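### The Section 11.0 footnote sets post-dose adverse event reporting at SAEs plus drug-related grade 2 or higher events, narrower than the primary safety objective and than what the protocol records

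*Protocol*

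**What the plan says.** The adverse event row of the Section 11.0 schedule carries a double-asterisk footnote with three rules.

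- SAEs are reported from consent to the day 45 ± 10 evaluation, whatever their cause.
- For other events after dosing: "Adverse events considered to be related to the drug that are grade ≥2 will be reported from the time of Illuminare-1 administration", up to the same end point.
- For events before dosing: "Adverse events from the time of informed consent to Illuminare-1 administration will be recorded in the medical history".

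Elsewhere the protocol collects more than this. Sections 4.1 and 15.0 have any adverse event after administration recorded and graded, with no minimum grade. Section 15.0 adds: "Following surgery, all adverse events will be evaluated at 10" days, and again at 30 and 45 days, each with its window. On cause, Section 4.1 says: "The adverse event will be assessed by the primary investigator to determine if the adverse event was caused by administration of the agent".

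On reporting, Section 4.2 (Part 1, item 9) says "Adverse events will be recorded and reported as necessary for the first 24 h after injection or until discharge" and then lists the later contacts; Part 2, item 4 is similar. Neither says what makes reporting necessary. The one per-cohort count that Section 15.0 names is of DLTs: "We will record the number of subjects in each cohort who experience a DLT after receiving Illuminare-1".

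**The concern.** Section 2.0 makes safety, measured by clinical evaluation, a primary objective of Part 1 and clinical safety assessment the primary objective of Part 2. Neither objective excludes mild events or events thought to come from surgery. The footnote filters non-serious events on both counts.

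Two features of the trial give this some weight.

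- **The expected signal may be mild.** Section 3.0 b) reports phototoxic potential in vitro and grade 1 erythema on unprotected skin of pigmented rats at 24 and 48 hours, which led to 48-hour precautions. It also reports administration-site damage in rats, at doses of 30 mg/kg or more. A mild human reaction of either kind would fall below the footnote's threshold.
- **Attribution is difficult.** The trial is open-label and single-arm, and every patient has just had a prostatectomy. An event caused by the agent but ascribed to surgery would fall outside the stated scope unless it was serious.

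At stake is how complete the published safety profile is for a first-in-human agent whose dose may rise from 0.25 to 2.25 mg/kg.

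**Working it through.** There is no plan figure to reproduce, because the point concerns the scope of a rule. The check sorts post-dose events by the footnote's own criteria and then looks for other text that widens the scope.

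**Step 1: what the footnote names.**

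| Post-dose event | Drug-related | Judged unrelated |
|---|---|---|
| Serious, any grade | Named for reporting | Named for reporting |
| Non-serious, grade 2 or higher | Named for reporting | Not named |
| Non-serious, grade 1 | Not named | Not named |

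Three of the four non-serious cells are outside the stated scope.

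**Step 2: does other text widen it?**

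- Section 4.2 (Part 1 item 9, Part 2 item 4): reporting as needed, with no criterion.
- Section 4.2 (day-30 call): events go to the principal investigator. This is internal and covers one contact.
- Section 10.0, item 12: "Patient will also receive a CTN telephone call within 2 days of surgery for toxicity evaluation". This is an assessment, with no reporting rule.
- Section 14.0: the rules count attributable grade 2 or higher toxicity. The only descriptive safety summary is change in the Neuropathy Impairment Scale.
- Section 15.0: DLTs are counted per cohort, and the DLT list has no grade 1 item.
- Section 15.1: submission requirements for SAEs only.
- Section 15.1.1.4: each cohort's safety parameters are assessed before escalation, and "Any trends towards treatment-related changes will be fully evaluated". This is a review by dose, but it requires no report.

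None of these requires the three unnamed cells to be reported.

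**Step 3: what is collected.** The schedule has 4 adverse event contacts per patient (under 24 h, and days 10, 30 and 45). With up to 50 patients that is 4 × 50 = 200 assessments. At the selected dose, 10 patients in Part 1 plus up to 20 in Part 2 make 30, so 4 × 30 = 120. These are counts of planned contacts and maxima, since the expansion may stop early. They are not counts of events left unreported. The documents give no human rate of mild or unrelated events, so no such count can be computed.

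**Step 4: do the rules depend on the unnamed events?** No. Escalation and stopping use attributable grade 2 or higher events, which the footnote does name.

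**The case against.** The best counter-argument is that reporting here means notification to oversight bodies, as in Section 15.1, and says nothing about the results tables, which a statistical analysis plan would normally define. The footnote is phrased around time windows and does not define the word.

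Part of this stands. A missing adverse event table would be no finding in a protocol, and the meaning of the word is open. But the oversight reading fits poorly. Section 15.1 requires submission of SAEs only, so it does not explain a rule for non-serious related events. Its SAE window also differs: it runs in general from the start of treatment to 30 days afterwards, while the footnote runs from consent to day 45 ± 10. And the footnote sits on the schedule row for adverse event assessment.

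A reader might also infer four stronger things that the documents do not support.

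- *That mild events are not captured.* They are: Sections 4.1 and 15.0 set no floor.
- *That the footnote forbids wider reporting.* It does not say that only these events are reported.
- *That one person alone decides attribution.* Section 4.1 gives the task to the primary investigator, but Section 4.2 uses a full neurologic assessment to judge relatedness, Section 15.1.1.1 involves the primary team for renal changes, and Section 15.1.1.4 mentions the safety monitoring board. Section 15.0 also groups possible with probable and definite causality, which narrows the unrelated group.
- *That escalation or stopping is compromised.* It is not.

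Neurotoxicity, the mechanism-based worry for a myelin binder, is the least affected: Section 4.2 has any change in the neurologic scores investigated, and Section 14.0 summarises the impairment scale without a grade threshold.

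**Conclusion.** The point holds as a modest, inexpensive improvement. The protocol states a reporting scope narrower than its own primary safety objective and than the events it already records and evaluates. Followed as written, the reported profile could omit non-serious grade 1 events and non-serious events judged unrelated. No dose choice, sample size, escalation step or stopping decision changes, and internal review would still see these events.

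This rests on two assumptions. The first is that reporting in the footnote means study reporting, which is the better reading but is not defined. The second is that no unseen analysis plan overrides it. The skin example further assumes that grade 1 erythema in rats is comparable with CTCAE grade 1 in patients, which the protocol does not establish. The size of the effect cannot be estimated from the documents.

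**What to change.** Amend the footnote so that all adverse events from Illuminare-1 administration to the day 45 ± 10 evaluation are reported by dose level, grade and attribution. State that drug-related grade 2 or higher events are shown as a separate subset and remain the basis of the escalation and stopping rules. The same amendment should say what reporting means, and Section 4.2 (Part 1 item 9, Part 2 item 4) should refer to it.

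The cost is a change to one footnote, two cross-references and modest extra data entry and tabulation, since adverse events are already assessed at each of the four contacts. No visit, patient or rule is added. The drawback is that expected surgical events will appear in the tables; showing attribution separately lets the reader set them apart. If that burden is judged too great, a fallback is to report skin, photosensitivity and injection-site events at any grade and attribution.

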## Investigational Agent Evaluations

Subjects will remain in-patient after administration of Illuminare-1 for 24 h before discharge. During this period, the patients will be monitored for adverse events according to CTCAE 5.0.

At 10 ( $\pm$  5) days, patients will be assessed during the routinely scheduled postoperative visit which may coincide with catheter removal. Patients will also be questioned about adverse events at 30 ( $\pm$  5) days via telephone, and at the first postoperative PSA lab assessment, which typically occurs around 7 weeks after surgery ( $45 \pm 10$  days).

The pharmacokinetics of Illuminare-1 will be evaluated from blood drawn at baseline, 15, 30, 120, 240, 480 minutes (all  $\pm$  10 min), 12 hours ( $\pm$  1h), 18 hours ( $\pm$  2h), and 24 hours ( $\pm$  2h) after injection in all patients. In addition, a minimum of 3 patients in each dose cohort will also have blood drawn at 48 hours ( $\pm$  24h) and 72 hours ( $\pm$  24h) after administration for pharmacokinetics evaluation. A minimum of 3mL whole blood will be collected into 5 mL EDTA purple top tubes. Handling instructions (e.g., sample processing, centrifugation, storage conditions) will be provided to the processing laboratory via SOP prior to sample collection. One tube of blood ( $<10$ cc) will be drawn and stored for potential future research investigations at in-person follow-up visits 10 days ( $\pm$  5 days) post-surgery and the first PSA blood draw ( $45 \pm 10$  days). The samples for future research will be taken under MSK IRB#06-107 or MSK IRB#12-245. All pharmacokinetics analyses will be performed using Phoenix WinNonLin (version 8.1) and a noncompartmental approach consistent with the intravenous route of administration. Pharmacokinetics model selection will be based on a visual inspection of goodness-of-fit plots (observations vs. predictions, residuals and weighted residuals vs. predictions). The assay values (concentrations vs. times) measured using a validated LC-MS method will be used to calculate half-life, volume of distribution, clearance, individual-specific elimination rate constant ( $K_e$ ), time to maximum concentration ( $T_{max}$ ), maximum concentration ( $C_{max}$ ), and area under the concentration–time curve (AUC) values. Pharmacokinetic analyses will be conducted at MSK by core facilities and the statistician will not perform these.

Pharmacokinetic blood sampling at 48 hours ( $\pm$  24 hours) and 72 hours ( $\pm$  24 hours) post injection as well as blood sampling for future research purposes at the Day 10 ( $\pm$  5 days) and Day 45 ( $\pm$  10 days) follow up visits may be obtained by The National Phlebotomy Provider Network (NPPN) when patients are not able to travel to an MSKCC facility or the MSKCC facility is closed. NPPN is a national medical specimen collection, processing, and delivery service. NPPN provides mobile medical specimen collection, processing, and delivery services to medical diagnostic laboratories, biotech companies, research organizations, medical practices, independent physician and non-physician practitioners, and individual patients under a physician's order.

NPPN will collect and process the specimen in accordance with specified protocols from the MSKCC laboratory. Additionally, NPPN will ship, deliver, or courier the specimens to the MSKCC laboratory in accordance with specified protocols from the MSKCC laboratory. In order

to coordinate these collections, the NPPN will have access to patient's name, address, and phone number.

Neurologic assessments will be performed at presurgery, before discharge from the hospital after surgery (approximately 24 h), and at in-person follow-up visits ( $10 \pm 5$  days and  $45 \pm 10$  days after surgery) using validated surveys. The battery of neurologic tests will be administered by the research team in coordination with and under the supervision of our co-investigators in the Neurology Division.

## **12.0 CRITERIA FOR REMOVAL FROM STUDY**

Patients will be withdrawn from the study if they express a desire to do so, if it is determined to be in the patient's best interest to do so, or if they do not undergo initiation of their surgical procedure. Given that patient involvement occurs only during the operation itself, we anticipate that very few (if any) patients will withdraw after consent. Patients who are not evaluable for either the safety or response endpoints will be excluded from the analysis and replaced.

Additional reasons for patient removal from the study include but are not limited to:

- Adverse events
- Abnormal laboratory values
- Protocol deviation
- Withdrawal of consent
- Death

Patients who withdraw from the trial due to either personal reasons or adverse events related to the study drug will be described in detail. Symptoms and, if applicable, follow-up testing related to the adverse event will be recorded during the hospital stay and at each follow up visit. All patients in this trial will undergo surgery, with a minimum hospital stay of 1 day; therefore, no patient should be lost to short-term follow-up. All patients will return at 10 (+/- 5) and 45 (+/- 10) days for postoperative visits. In the unlikely event that patients are lost to follow-up, they will be contacted by telephone.

